# The effectiveness of intra-articular vs subacromial corticosteroid injection for frozen shoulder

**DOI:** 10.1097/MD.0000000000019706

**Published:** 2020-04-17

**Keywords:** corticosteroid injection, frozen shoulder, intra-articular, randomized controlled trial, study protocol, subacromial

## Abstract

**Background::**

Intra-articular (IA) corticosteroid injection is a commonly used therapy for frozen shoulder (FS), but controversy still exists regarding the injection site with the best outcome. This randomized controlled trial is designed to determine whether corticosteroid injection into the subacromial space was not inferior to IA injection in patients with FS.

**Methods::**

This study will be a single-center, randomized, and double-blinded trial. Sixty patients who meet inclusion criteria will be randomized in a ratio of 1:1 to either subacromial injection or IA injection group. The outcome evaluations will be conducted at 4 time points (baseline, 4, 8, and 12 weeks after the injection) by an independent physical therapist. The primary outcome measure is visual analog scale for pain, whereas the secondary outcomes include Constant score, and shoulder passive range of motion including abduction, forward elevation, external rotation at the side, and internal rotation at the side.

**Discussion::**

This study has limited inclusion and exclusion criteria and a well-controlled intervention. This clinical trial is expected to provide evidence of proper site of corticosteroid injection for the treatment of FS.

**Trial registration::**

This study protocol was registered in Research Registry (researchregistry5368).

## Introduction

1

Frozen shoulder (FS), a painful condition with gradual onset in the glenohumeral joint, is a common cause of shoulder disability.^[1]^ It has been reported the yearly prevalence of FS in general population to be 2.4/1000.^[2,3]^ FS is considered as a self-limited process from synovial inflammation to capsular fibrosis with three overlapping phases: the freezing phase (2–9 months), the stiffening phase (4–12 months), and the thawing phase (12–42 months).^[4]^ Typically, severe pain occurs mainly in the first 2 stages, and most patients can relieve pain and restore activity within 1 to 2 years after the onset of disease, but some residual joint stiffness may remain.^[5]^ Although the exact etiology have not yet been well understood, factors such as age, diabetes, autoimmune diseases, and trauma may associate with FS.^[6,7]^

Two most commonly used treatments for FS are physical therapy and local steroid injections. Combining injection with physical therapy may improve the efficacy in the treatment of shoulder stiffness.^[8]^ Triamcinolone acetonide is a well-known long-acting corticosteroid. Early treatment with local injection may reduce synovial inflammation, which leads to a decrease in pain perception and early acceleration of functional recovery. Several previous systematic reviews reported the effects of corticosteroid injections better than physiotherapy or placebo within 6 weeks, but effect on long-term follow-up is uncertain.^[9,10]^

However, various injection techniques, such as subacromial (SA) injection, intra-articular (IA) injection, and rotator interval injection are commonly used by orthopedic surgeons, primary care physicians, and rheumatism doctor. The argument on the best injection sites remains to be resolved. Some randomized controlled trials have reported similar effects between the IA and SA treatments,^[11,12]^ the other 2 randomized controlled trials claimed the superiority of IA injection up to 12 weeks for pain relieve and functional recovery compared to SA injection.^[13,14]^ With injection of 40 mg of triamcinolone and 2 mL 2% lidocaine, Kim et al found RI injection was superior to IA in the early phase of FS.^[15]^

Therefore, a prospective, randomized study will be designed to compare short-term outcomes between SA and IA corticosteroid injections in patients with primary FS. The aim of current study is to reveal which treatment modality is superior in terms of the visual analog scale (VAS) score for pain as well as functional outcomes, including constant score, and range of motion (ROM). We hypothesized that corticosteroid injection into the SA will provide similar clinical outcomes compared with IA.

## Material and method

2

### Study design

2.1

This single center, double-blinded, randomized controlled trial is conducted in accordance with the Declaration of Helsinki principles. The study will be conducted in the Affiliated Hospital of Shandong Academy of Medical Sciences from March 01 2020 till February 28 2021. The study protocol was approved by local ethics committee board (BZSY-2020KYKTPJ-07) and subsequently registered in Research Registry (researchregistry5368). The flowchart of this trial is shown in Figure 1.

**Figure 1 F1:**
[figure not shown]
Flow diagram of the study.

### Recruitment and consent

2.2

All patients with FS will visit articular orthopedic outpatient at our hospital, where they will be invited to participate the study by treating surgeon. The surgeon will introduce the specific content of the trial and then answer all of patient's questions patiently. Meanwhile, a written information about our trial will be provided to the patient. Written informed consent will be required if the patient agrees to participate in the study. It is acceptable to withdraw from the study at any time because patient participation is voluntary.

### Randomization and blinding

2.3

After the signing of the informed consent, each participant will then be randomly assigned to IA and SA groups according to a randomization list generated by computerized random-number generator. The injection allocations are printed on cards and inserted into sealed, opaque envelopes. An independent member of the study group, who do not know treatment details, will conduct the allocations.

### Participant selection and eligibility criteria

2.4

The inclusion criteria require the following:

(1)Adults between the ages of 20 and 70 years;(2)Patients were diagnosed with primary FS with a normal finding on radiography of the affected shoulder;(3)passive motion restriction of glenohumeral joint greater than 30 degrees in at least 2 planes of movement;(4)stage 2 of FS defined by Hannafin and Chiaia with a pain duration of less than 9 months and VAS score ≥3 for shoulder pain.^[6]^

The exclusion criteria require the following:

(1)FS secondary to rheumatic diseases, infectious arthritis, and tumor; infections; rotator cuff disease; osteoarthritis of the glenohumeral joint; fibromyalgia; shoulder fractures; bilateral FS;(2)patients who received corticosteroids injection on the affected side in the previous 3 months;(3)inability to understand and cooperate with the investigators or to give valid consent.

### Intervention

2.5

With the patients sit in an upright position, all injections will be performed by a senior physician with many years of experience in ultrasound-guided injections. The physician is informed about the purpose of study, but patients do not know which injection they will receive. Before injection, adequate iodophor sterilization is carried out around the injection site. 4 mL 2% lidocaine is injected into specified site to anesthetize the skin, followed by 40 mg/mL triamcinolone under ultrasonographic guidance. The IA injection is from the posterior portal and guide into the joint by ultrasonography, while the SA injection is from the lateral portal and guide into the SA space. During the injection, a 25-gauge, 3 cm-long needle is aspirated properly to ensure that the needle is not placed in a blood vessel. Ultrasound imaging confirm the location of the needle. All participants have to stay in the outpatient operating room of hospital for at least 20 minutes to detect and record any acute adverse reactions after the injection including dizziness, skin flushing, and local bleeding. Late adverse events including menstrual disorder, infections, character change, and skin pigmentation will be also checked at follow-up. After the injection, a handbook for rehabilitation programs will be handed out to instruct the patients strengthen functional exercise of shoulder joint. In addition, any additional medication or physical therapies will be also prohibited.

### Clinical evaluation

2.6

The outcome evaluations will be conducted at 4 time points (baseline, 4, 8, and 12 weeks after the injection) by an independent physical therapist who is blinded to the injection treatments performed. Data will be collected to allow a determination of VAS score for shoulder pain, Constant score, and shoulder passive ROM. The primary outcome is 10-cm VAS score with 0 cm as “no pain” and 10 cm as “the worst imaginable pain”. With patients in the seated position, the passive shoulder ROM, including abduction, forward elevation, external rotation at the side, and internal rotation at the side are measured using a standard goniometer with a scale marked in 1° increments. The examiner moves shoulders slowly and measure 3 times for each shoulder, then the mean angle is used for statistical analysis.

### Sample Size

2.7

The required sample size in each group are confirmed beforehand by power and sample size calculation. In a previous study conducted by Sun et al,^[12]^ the response within each subject group was normally distributed with standard deviation 3.0 and a significant difference in VAS score at 12 weeks was 2.4. The analysis reveals that a total number of 48 patients (24 patients in each group) are required to provide a power of 80%. The Type I error probability associated with this test of this null hypothesis is 0.05. Accounting for potential loss to follow-up of 20%, we aim to enroll 30 participants per group.

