## Discussion

3

FS is a common shoulder disorder characterized by gradually increasing pain of spontaneous onset and limitations on the range of glenohumeral motions.^[1]^ Although extensive clinical and laboratory studies have been performed, the exact etiology, natural course, and pathophysiology of FS are not yet well understood. FS has been considered as a sequential pathologic process from synovial inflammation to capsular fibrosis.^[16–18]^ An inflammation cascade precipitated by abnormal expression of inflammatory cytokines is thought to be followed by abnormal tissue remodeling and pathologic fibrosis in FS.^[19]^ These heterogeneous stages and the absence of widely-accepted diagnostic criteria have led to controversial results.

Additionally, the nature of the pathologic lesion remains debatable. Typical FS magnetic resonance imaging findings are enhancement and increased thickness of the joint capsule in the axillary recess and rotator interval, including the coracohumeral and superior glenohumeral ligaments.^[20]^ A positron emission tomography/computed tomography study in FS also demonstrated hypermetabolic lesions in the rotator interval, anterior joint capsule, and axillary recess.^[21]^ Although it is clear that the capsule of the glenohumeral joint is involved in the pathogenesis of FS, the results from recent studies revealed that the SA bursa may be a pathologic lesion or a therapeutic target. Lho et al reported that inflammatory cytokines were elevated in the SA bursa of FS, suggesting that the SA bursa may be associated with the pathogenesis of FS.^[22]^ Fluid collection, increased vascularity, or enhancement of the SA bursa on magnetic resonance imaging or ultrasound may be visible in idiopathic FS.^[1]^ In a clinical setting, inflammation of the SA bursa, as well as the joint capsule, can be detected during arthroscopic surgery in patients with refractory FS. Some clinical trials have reported that corticosteroid injection into the SA bursa had an effect similar to that of IA injection in the treatment of idiopathic FS.^[13–15]^ These results suggested that the SA bursa may be a potential pathologic lesion in idiopathic FS. However, there is no clear explanation as to whether the SA bursa is a major or minor clinical lesion. The aim of current study is to compare the short-term effects of corticosteroid injections into different sites, including the IA and SA.

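### The 2.4 cm planning difference is credited to a study that the Introduction cites for similar effects of the two injections, so it is unsupported as written; the stated 80% power is also slightly favourable

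*Protocol article*

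**What the plan says.** Section 2.7 (Sample Size) bases the calculation on one earlier study, reference 12. From it come the spread, "the response within each subject group was normally distributed with standard deviation 3.0", and the difference, "a significant difference in VAS score at 12 weeks was 2.4". With a type I error of 0.05 and 80% power the section arrives at 24 patients per group (48 in total), raised to 30 per group for 20% loss to follow-up. No other basis for the difference is given.

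The Introduction puts reference 12 on one side of a disagreement in the literature: "Some randomized controlled trials have reported similar effects between the IA and SA treatments,^[11,12". On the other side it places references 13 and 14: "the other 2 randomized controlled trials claimed the superiority of IA injection up to 12 weeks". It then states the trial's own expectation: "We hypothesized that corticosteroid injection into the SA will provide similar clinical outcomes compared with IA".

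The Discussion cites references 13 to 15 for the statement that "corticosteroid injection into the SA bursa had an effect similar to that of IA injection in the treatment of idiopathic FS.^[13–15".

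**The concern.** The trial compares IA with SA injection on VAS pain, and 12 weeks is its last assessment. A significant 12-week VAS difference of 2.4, used to size such a trial, reads naturally as the IA-versus-SA difference in the cited study. The Introduction counts that same study among those in which the two injections did about equally well. For one contrast, these descriptions exclude each other.

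The sample size has no other stated support. If 2.4 came from a different comparison, such as a change within a group, or belongs to a different reference, then section 2.7 gives the reader no reason to expect or target 2.4 cm between these two arms. This matters more here because the trial expects similar outcomes. A non-significant result would look like confirmation, so readers need to know what size of difference the trial could have detected and where that figure comes from.

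**Working it through.** **Inputs, all from section 2.7:** difference d = 2.4 cm, SD = 3.0, type I error 0.05, power 80%, 24 evaluable per group, 20% loss. The section does not say whether the test is two-sided. Two-sided is assumed because it comes closest to the stated figure; one-sided 5% would need only 20 per group.

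**Reproducing the stated figure (normal approximation).**

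n per group = 2 × [SD × (1.960 + 0.842) / d]² = 2 × (3.0 × 2.802 / 2.4)² = 24.53, rounded up to 25.

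The stated 24 is this value rounded down. Power at 24 per group:

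- Standard error of the difference = 3.0 × √(2/24) = 0.866.
- 2.4 / 0.866 = 2.771, and 2.771 − 1.960 = 0.811.
- Power = Φ(0.811) = 79.1%.

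Enrolment: 24 / (1 − 0.20) = 30 per group, as stated.

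**The same check with the two-sample t test.** With 46 degrees of freedom, noncentrality 2.771 and critical value 2.013, power at 24 per group is 77.4%. The smallest n that reaches 80% is 26 per group (80.8%). So neither method gives 80% at 24, but the shortfall comes from rounding and choice of method and is small. If all 30 per group were evaluable, power at 2.4 cm would be 87% (normal) or 86% (t).

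**What 24 per group detects with 80% power.** Normal approximation: 2.802 × 0.866 = 2.43 cm. t test: 2.48 cm, or about 2.5 cm.

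**Power if the true difference is smaller.** The document gives no smaller target, so the differences below 2.4 cm are assumptions shown as a range (SD 3.0, two-sided 5%, 24 per group).

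| True difference (cm) | Normal | t test |
|---|---|---|
| 2.4 | 79.1% | 77.4% |
| 2.0 | 63.7% | 61.8% |
| 1.5 | 41.0% | 39.6% |
| 1.0 | 21.0% | 20.4% |

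The 95% confidence interval for the difference would have a half-width of 2.013 × 0.866 = 1.74 cm. Even an observed difference of zero would be compatible with true differences of up to 1.74 cm in either direction.

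**Roles given to the references.**

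| Reference | Introduction | Section 2.7 | Discussion |
|---|---|---|---|
| 12 | IA and SA similar | significant 12-week VAS difference of 2.4 | not cited on this point |
| 13, 14 | IA superior up to 12 weeks | not used | SA similar to IA |
| 15 | rotator interval better than IA in the early phase | not used | SA similar to IA |

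The row for reference 12 is the one that affects the sample size.

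**The case against.** The strongest reply is that section 2.7 names no contrast. A study can find IA and SA similar and still report a significant 2.4 for something else, or 2.4 may have been meant as a difference worth detecting. This stands as a limit on the conclusion: a reader might infer that 2.4 is proven wrong, or that reference 12 showed no such difference, and the document supports neither. It does not remove the problem. Section 2.7 presents 2.4 as a result of the cited study, beside its SD, and offers no argument that 2.4 is clinically important. If it came from another contrast, its use as a between-arm difference still needs a reason.

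A second reply is that the reference numbering may have slipped, so that 2.4 is correctly sourced under another number. The conflicting accounts of references 13 and 14 make this plausible. It is one of the things that reconciling the citations would settle. By the same token, the conflict over references 13 to 15 is not evidence against 2.4, because section 2.7 uses none of them.

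Third, the calculation essentially reproduces, and the lower powers at smaller differences would apply to any trial of this size and spread. Both are true. Those powers describe what the trial can show; they do not follow from the citation conflict. Nor can one say that any smaller difference would usually be missed: that holds at 1.5 cm and below, but at 2.0 cm power is still about 62%.

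A reader might also set 2.4 against the entry criterion of "VAS score ≥3 for shoulder pain" and call it implausibly large. That does not follow. The criterion is a minimum, and the document gives no expected baseline mean.

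**Conclusion.** The point holds in a limited form. Reference 12 is cited in the Introduction for similar effects of IA and SA and in section 2.7 for a significant 12-week VAS difference that sizes an IA-versus-SA trial. The planning difference is therefore unsupported as written. Which statement is wrong cannot be decided from the document.

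The numerical fault is small: 24 per group gives 79% (normal approximation) or 77% (t test) where 80% is stated, and 25 or 26 per group would be needed. These figures assume SD 3.0 and a two-sided 5% test. On the t test, 80% power is reached at about 2.5 cm.

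The disagreement between the Introduction and the Discussion over references 13 to 15 is a secondary, editorial matter.

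**What to change.** In section 2.7:

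- Reconcile the two uses of reference 12, correcting the citation if the number is wrong, and state which comparison in the source gave 2.4 and 3.0.
- If that comparison was not IA versus SA, do not present 2.4 as the difference expected from that study. State instead that 24 evaluable patients per arm give 80% power for a difference of about 2.5 cm, and about 77% for 2.4 cm (two-sided 5% t test, SD 3.0).
- Add that a non-significant result does not rule out smaller differences.

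As a secondary wording point, make the Introduction and the Discussion agree on what references 13 to 15 each showed.

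The cost is rewording in the Introduction, section 2.7 and the Discussion, and a slightly less favourable stated power. Enrolment stays at 30 per group.

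### Section 2.7: on the printed inputs, 24 evaluable patients per group give about 77% to 79% power rather than the stated 80% (minor correction)

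*Protocol article*

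**What the plan says.** All the figures are in section 2.7 (Sample Size) of the protocol article. The variability comes from an earlier study: "the response within each subject group was normally distributed with standard deviation 3.0". The effect comes from the same source: "a significant difference in VAS score at 12 weeks was 2.4". On error rates, the section says "The Type I error probability associated with this test of this null hypothesis is 0.05". The result is that "a total number of 48 patients (24 patients in each group) are required to provide a power of 80" per cent, and the last step is "Accounting for potential loss to follow-up of 20%, we aim to enroll 30 participants per group". The abstract gives equal allocation: patients "will be randomized in a ratio of 1:1 to either subacromial injection or IA injection group".

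The section does not name a test or formula, and it does not say whether the 5% is one-sided or two-sided.

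**The concern.** Section 2.7 prints every input needed to recompute its sample size except the sidedness and the formula. A reader who does so under the usual conventions does not arrive at 24 per group. Two-sided, 24 is slightly too few; one-sided, it is more than needed.

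The 24 is also the base for the enrolment target. If the true requirement is 25 or 26, the allowance for 20% loss is not fully covered: a trial that loses exactly the planned fraction ends a little under its stated power. What is at stake is the accuracy of the power statement and of the loss the design can absorb. The viability of the trial is not in question.

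**Working it through.** **Inputs.** Difference δ = 2.4, SD σ = 3.0, type I error 0.05, power 80%, loss 20% (all section 2.7); allocation 1:1 (abstract, Methods). Sidedness is not stated; two-sided is assumed first. The standardised difference is δ/σ = 2.4/3.0 = 0.80.

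**Step 1. The plan's own figure, normal approximation, two-sided 5%.**
n per group = 2(z₀.₉₇₅ + z₀.₈₀)²/(δ/σ)² = 2(1.960 + 0.842)²/0.64 = 24.53, which rounds up to 25.
Power at 24 = Φ(0.80·√(24/2) − 1.960) = Φ(2.771 − 1.960) = 79.1%.
This is the closest reading. The printed 24 follows only if 24.53 is rounded down, which leaves power just under the target.

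**Step 2. Two-sample t-test, two-sided 5%** (noncentral t, 2n − 2 degrees of freedom). Solving for 80% power gives n = 25.52, so 26 per group.

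| Evaluable per group | t-test power |
|---|---|
| 24 | 77.4% |
| 25 | 79.1% |
| 26 | 80.7% |
| 28 | 83.6% |
| 30 | 86.1% |

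**Step 3. One-sided 5%.** The normal approximation needs 20 per group. The t-test gives n = 20.03, so 21. With 24 per group, power would be about 87% (normal) or 86% (t-test), so 24 would not be the number required for 80%.

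**Step 4. Allowance for loss.** 24/(1 − 0.20) = 30, so the inflation step itself is right. With 30 enrolled per group:
- the planned 20% loss is 6 patients and leaves 24;
- 26 evaluable allows a loss of 4 of 30 = 13.3%;
- 25 evaluable (normal approximation) allows a loss of 5 of 30 = 16.7%.

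**Step 5. Could rounding of the inputs explain 24?** Both inputs are printed to one decimal.
- Normal approximation: δ = 2.449 with σ = 3.0 gives n = 23.56, so 24; δ = 2.4 with σ = 2.951 gives 23.73, so 24.
- t-test: δ = 2.449 with σ = 2.951 gives 23.79, so 24, with power 80.4%. Here both inputs have to lie near the edge of their rounding range.
- Rounding can also work the other way: δ = 2.35 with σ = 3.0499 gives 27 (normal) or 28 (t-test).

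Unrounded values could therefore give 24, but the printed ones do not.

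**The case against.** The strongest reply is that nothing material is wrong. The protocol does not say that a t-test was used. By the normal approximation the requirement is 24.53 and power at 24 is 79.1%, which is half a patient per group and 0.9 of a percentage point from the claim. The inputs are borrowed from one earlier study and printed to one decimal, so 24 may have been correct for the unrounded values. The shortfall also appears only when most of the loss allowance is used: by t-test, power is 86.1% with no loss and still above 80% with 26 evaluable per group. The uncertainty in a borrowed SD is likely to outweigh all of this.

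Most of this stands, and it limits the point to a minor one. It does not remove it. A required sample size is rounded up, because rounding down misses the target by construction. The t-test is the natural match for a normally distributed response whose SD has to be estimated, and there the gap is 2.6 points. The reader has only 2.4 and 3.0 to work from, and rounding could as easily raise the requirement as lower it.

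A reader might go further and infer that the trial is underpowered and must enrol more: 26/0.8 = 32.5, so 33 per group or 66 in total. The document does not support that. The figure depends on a test the protocol does not name, it assumes the full 20% loss occurs, and it would add patients to recover 2.6 points of power at most.

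**Conclusion.** Wrong as written, and minor. On the printed inputs and a two-sided 5% level, 24 evaluable patients per group fall short of the stated 80% power by 0.9 points (normal approximation) or 2.6 points (t-test). The requirement is 25 or 26 per group, that is 1 or 2 more than stated.

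This rests on two assumptions: that the test is two-sided, and that 2.4 and 3.0 are the values actually used. If the test were one-sided at 5%, the stated 24 would exceed the requirement; it would still not match the inputs, but power would not be short. If unrounded source values were used, 24 may be right and the printed inputs incomplete.

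The arithmetic check takes the calculation as section 2.7 frames it, as detection of a difference. The abstract's non-inferiority aim raises a separate question that this point does not settle.

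**What to change.** Keep 60 patients. In section 2.7, name the test and its sidedness and restate the power. For a two-sided t-test the text could read:

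> With a two-sided 5% t-test, 24 evaluable patients per group give about 77% power for a 2.4 cm difference with SD 3.0. Power of 80% needs 26 evaluable per group, which 30 enrolled per group provide if loss is no more than about 13%. With no loss, power is about 86%.

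If the normal approximation was intended, the matching figures are 79% at 24 per group, and 25 per group for 80%. If the calculation used unrounded values from the earlier study, print those values, so that the stated 24 can be reproduced.

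Basing the power on a baseline-adjusted analysis is not proposed as a remedy, because it would need a correlation between baseline and 12-week VAS that the document does not give.

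The cost is a few corrected sentences and a slightly less favourable power statement. Enrolment, conduct and analysis do not change.
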